**Fig. 1 Fig1:**
[figure not shown]
SMARTChip technology

The SMARTChip assay could be used to triage patients with suspected stroke symptoms into those people likely to have a non-stroke mimic condition and those likely to have true stroke. The assay may have maximum impact if deployed pre-hospital but may also be of use on arrival at hospital for patients who do not present to the ambulance service, or if the technology is not available in the ambulance or was not deployed by ambulance practitioners because stroke was not suspected. In both settings, the assay result would be useful for determining whether patients with suspected stroke symptoms continue along the stroke emergency assessment pathway or whether they should be directed to other more appropriate emergency services for further assessment and treatment (i.e. the test result indicates that a patient is likely to have a non-stroke mimic condition).

The SMARTChip assay may also have an alternative purpose in the context of suspected stroke. Due to the greater volume of brain tissue involved during LVO stroke, it is hypothesised that WBPC readings will be elevated higher and for a longer time period when compared to both mimic conditions and those stroke patients without LVO. Sequential SMARTChip assay readings may therefore be able to assist in identification of patients with LVO stroke. As time-critical mechanical thrombectomy treatment is only available in a small number of regional neuroscience centres (comprehensive stroke centres), patients with LVO suitable for thrombectomy typically require secondary transfer from a HASU. Rapid identification of mechanical thrombectomy-eligible patients could facilitate transfer and expedite access to treatment.

The main aim of this study is to evaluate the diagnostic accuracy of the SMARTChip assay for identification of stroke mimic conditions amongst the suspected stroke population when used in either the pre-hospital or hospital environment. An exploratory substudy will be conducted to assess whether serial WBPC values could be useful for the identification of LVO stroke.

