### Study design

Two prospective blinded observational cohort studies will be conducted, one involving a convenience series of suspected stroke patients tested by hospital services and one involving a convenience series of suspected stroke patients tested by ambulance services. There will be 5 phases:
Phase 1: pilot cohort study in hospital to review key technical performance parameters of the SMARTChip assayPhase 2: main hospital cohort study part 1. Once agreement is reached that technical performance is satisfactory, data will be collected to determine the diagnostic accuracy of WBPC assay readings for identification of mimic conditions (objective 2) and to build the statistical model (objective 3).Phase 3: main hospital cohort study part 2. Data will be prospectively collected to confirm the diagnostic accuracy of (i.e. validate) the hospital statistical model (objective 4).Phase 4: ambulance cohort study part 1. Data will be collected to determine the diagnostic accuracy of WBPC assay readings for identification of mimic conditions (objective 1) and to build the statistical model (objective 3).Phase 5: ambulance cohort study part 2. Data will be prospectively collected to confirm the diagnostic accuracy of (i.e. validate) the ambulance statistical model (objective 4).

Phases 4 and 5 may overlap with phases 2 and 3 depending on logistical factors, e.g. time taken to commence ambulance service involvement or availability of sufficient testing equipment.

Data collection to report the failure rate of the SMARTChip assay will run across phases 2–5. Data collection for the substudy is relevant to phases 4 and 5 only.

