### Sample size

Pilot study. There is no pre-specified sample size for the hospital pilot study. This phase will continue until agreement is reached about technical performance parameters as described below.Hospital cohort study. In the hospital setting, we consider that test specificity for mimics is more important than sensitivity such that mimics are directed away from the emergency stroke pathway whilst minimising removal of stroke patients in error. To detect a 90% (lower 95% confidence limit, 80%) diagnostic specificity for mimic identification assuming a mimic rate of 25% (i.e. 75% non-mimic or true stroke patients), one-tailed 5% type I error rate and 90% power, 167 participants (125 non-mimics) are required for the ‘per-protocol’ analysis. For validation of the hospital statistical model (combined clinical data and SMARTChip assay reading), 100 further non-mimics are needed, i.e. a further 134 patients in total. This gives a sample size of 301 (225 non-mimics). However, this target anticipates a non-mimic rate of 75% in the test population. If the mimic rate is higher, additional patients will be required. Inflating for 20% for participants who cannot feature in the ‘per-protocol’ analysis (see definition below in ‘Main hospital and ambulance study analyses’) gives an initial target sample size of 377 participants (including 281 non-mimics).Ambulance cohort study. In the pre-hospital setting, we consider that test sensitivity for mimics is more important than specificity to maximise removal of mimics from the emergency stroke pathway for service efficiency. To detect an 88% (lower 95% confidence limit, 80%) diagnostic sensitivity for mimic identification assuming a mimic rate of 40%, one-tailed 5% type I error rate and 90% power, 498 study participants (199 mimics) are required for the ‘per-protocol’ analysis (Agresti-Coull method [25]). For validation of the statistical model (combined pre-clinical data and SMARTChip assay reading), 100 further mimics are needed [26], i.e. a further 250 patients in total. This gives a sample size of 748 (299 mimics). However, this target reflects a typical FAST mimic rate of 40% amongst suspected stroke admissions. If the mimic rate is lower, additional patients will be required. Inflating for 20% of participants who cannot feature in the ‘per-protocol’ analysis (see definition below in ‘Main hospital and ambulance study analyses’) gives an initial target sample size of 935 patients (including 374 mimics).

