Sub-study objective 1: to explore the diagnostic accuracy of two sequential SMARTChip assay WBPC readings for identification of large vessel occlusion stroke using a reading obtained in the pre-hospital setting and a second reading obtained in the hospital setting

This analysis will include only patients who have both a pre-hospital- and hospital-verified WBPC reading, a reference standard assigned and who meet all the eligibility criteria for both tests.

Logistic regression analyses with diagnosis (LVO) as the outcome, hospital WBPC reading as the explanatory variable and pre-hospital WBPC reading as a covariate will be used to construct a receiver operating curve (ROC) for all possible test thresholds. Area under the ROC curve and optimal sensitivity, specificity, and negative and positive predictive values will be reported with 95% confidence intervals (CI). As for the main in-hospital study, the optimal threshold will be chosen to maximise specificity.
b)Sub-study objective 2: to develop and retrospectively explore the diagnostic accuracy of a statistical model which combines routinely available clinical data with pre-hospital- and hospital-obtained SMARTChip WBPC readings to predict the presence of large vessel occlusion.

Key variables will be added to the model described above to determine if this could significantly increase its accuracy. Clinical variables that would be available to ambulance and/or hospital staff will be included to reflect those available at the point of testing. Multivariate logistic regression will be conducted, with diagnosis (LVO) as the outcome and pre-hospital and hospital WBPC readings along with variables considered to be of possible clinical importance (such as blood pressure, pre-hospital FAST symptoms, NIHSS) as the explanatory variables. A stepwise variable selection procedure will be used, and only variables that significantly improve the ROC AUC will be retained in the model. Sensitivity, specificity, ROC AUC (with confidence intervals) and threshold will be reported if a suitable model is found. As for the main in-hospital study, the optimal threshold will be chosen to maximise specificity.
c)Substudy subgroup and exploratory analyses

Contingent on the results of the study, it may be important to carry out some data-driven subgroup or exploratory analysis. These will be determined post hoc and reported as such.

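### The LVO model in sub-study objective 2 is selected, fitted, thresholded and scored in the same patients, with no validation phase and no optimism correction stated in the article, so its reported accuracy will tend to be too high

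*Protocol article*

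**What the plan says.** Sub-study objective 2 (Statistical analyses, item 7) sets out to "develop and retrospectively explore the diagnostic accuracy of a statistical model which combines routinely available clinical data" together with the two purine readings, with LVO as the outcome. The candidate list is open: blood pressure, FAST symptoms and NIHSS are given as examples. Selection is stepwise, and a variable stays only if it significantly improves the AUC; no significance level is given. The threshold is then chosen to maximise specificity. Sensitivity, specificity, threshold and AUC with confidence intervals are reported if a suitable model emerges.

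On the source of the data, Study design says: "Data collection for the substudy is relevant to phases 4 and 5 only". The two phases are not split for the LVO model. Phase 5 exists to "confirm the diagnostic accuracy of (i.e. validate) the ambulance statistical model (objective 4", which is the mimic model, and phase 3 does the same for the hospital mimic model. The Sample size section adds patients for validating the mimic models only (ambulance cohort: "100 further mimics are needed [26], i.e. a further 250 patients in total"). It gives no sample size for the substudy.

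The substudy's status is stated at the end of the Background: "An exploratory substudy will be conducted to assess whether serial WBPC values could be useful for the identification of LVO stroke".

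**The concern.** A model scored on the patients used to choose its variables, coefficients and cut-off looks better than it will in new patients. Here selection works on AUC, which is also the headline measure reported, so the upward bias is built into the procedure. Reporting only when a suitable model is found filters further towards favourable results.

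The authors guard against this for the mimic models with separate validation phases and extra patients. The LVO model has the same structure, probably with far fewer events, and lacks that protection.

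What is at stake is how readers judge LVO detection. The Discussion presents it as a possible alternative use of the test, and the figures from this objective are the ones on which its promise would be judged.

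**Working it through.** **1. The plan's own figure: the pool that feeds the substudy.** Only the ambulance cohort supplies substudy patients. Inputs from Sample size: a target sensitivity of 0.88, a lower limit of 0.80, and the design values in this statement: "assuming a mimic rate of 40%, one-tailed 5% type I error rate and 90% power, 498 study participants (199 mimics) are required".

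- Mimics needed for 0.88 against 0.80, one-sided 5%, 90% power: an exact binomial calculation gives 198. At 199 the exact test has alpha 0.046 and power 0.922, so the stated 199 is reproduced to within one.
- Participants: 199 / 0.40 = 497.5, rounded up to 498.
- Validation of the mimic model: 100 / 0.40 = 250; 498 + 250 = 748.
- Inflation: 748 / (1 − 0.20) = 935, as stated ("gives an initial target sample size of 935 patients (including 374 mimics").

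The stated size holds. It is built on mimics, not on LVO cases.

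**2. How many LVO cases might there be?** The article does not say, so this step rests on assumptions. The nearest figure is in the Background, where thrombectomy for LVO is put at 5–10% of patients. That is not an LVO prevalence for the substudy. Taking it as one:

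- Non-mimics among 748: 748 × 0.60 = 448.8.
- LVO at 5%: 448.8 × 0.05 = 22.4. At 10%: 448.8 × 0.10 = 44.9.
- If only half have a verified second reading: 11.2 to 22.4.

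Several rules push the count down. The second reading depends on trained hospital staff being available, and must be taken within 6 h of onset and before reperfusion treatment (Study participants). Both readings must be verified. Ischaemic strokes with NIHSS above 5 but no angiography leave the LVO analyses (Reference standards, Substudy).

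One rule may push it up: LVO is defined as a Clot Burden Score below 10, possibly a wider group than thrombectomy patients. Reaching 75 to 100 cases would need 75 / 448.8 = 16.7% to 100 / 448.8 = 22.3% of non-mimics, all with a verified second reading.

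**3. Size of the optimism.** Optimism = apparent AUC in the development data − true AUC of the fitted model in the population. It was simulated with 200 runs per setting, independent normal predictors, both purine readings forced in, and backward AIC elimination for the rest. AIC stands in for the article's AUC rule, which is not defined closely enough to program. Settings with 22 cases used 374 or 748 patients; the others used 748. Two examples:

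- 12 candidates, 45 LVO, underlying AUC 0.75: 0.773 − 0.723 = 0.050.
- 20 candidates, 22 LVO of 374, underlying AUC 0.75: 0.819 − 0.683 = 0.136.

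| Candidates | LVO cases | Optimism, underlying AUC 0.85 | Optimism, underlying AUC 0.75 |
|---|---|---|---|
| 8 | 22 | 0.036–0.041 | 0.065–0.070 |
| 8 | 45 | 0.021 | 0.037 |
| 12 | 22 | 0.050–0.056 | 0.086–0.088 |
| 12 | 45 | 0.028 | 0.050 |
| 20 | 22 | 0.078–0.092 | 0.124–0.136 |
| 20 | 45 | 0.046 | 0.075 |
| 8 | 75–100 | 0.011–0.014 | 0.020–0.024 |
| 12 | 75–100 | 0.015–0.018 | 0.027–0.032 |
| 20 | 75–100 | 0.027–0.034 | 0.044–0.055 |

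For 22 to 45 cases and 8 to 20 candidates the range is 0.021 to 0.136. For 75 to 100 cases it is 0.011 to 0.055. With only 10 cases it rises to 0.088 to 0.258. It was positive in every setting. Optimism in sensitivity and specificity at the chosen threshold was not simulated.

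**The case against.** The strongest reply is that this is an omission from a condensed article. It names no resampling method and no method for the confidence intervals, and both are often left to an analysis plan, which is not shown. The authors also label the substudy exploratory and the evaluation retrospective, and keep the word prospective for the mimic models. They appear to have separated a validated main aim from unvalidated exploration on purpose.

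Part of this stands. A reader might infer that no correction will be made at all, but the documents support only that none is stated in this article. A reader might also infer that the substudy decides whether LVO detection is pursued. No go/no-go rule or success criterion for LVO appears anywhere.

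Nor do the documents support an inflated AUC with a narrow interval. In illustrative settings with small LVO counts, Hanley–McNeil 95% intervals around the apparent AUC are wide: 0.71 to 0.97 for an AUC of 0.838 with 15 LVO of 200, and 0.74 to 0.90 for 0.818 with 40 of 400. Each contains the corresponding mean true AUC (0.752 and 0.774).

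What does not stand is that the labels settle the matter. The sequence of selection, fitting, threshold and scoring in one data set is written into the text. The words exploratory and retrospective do not tell a reader how large the bias is, and they do not correct the reported numbers. A wide interval still centres on an optimistic value unless it is built to reflect the selection and threshold steps.

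**Conclusion.** The point holds with limited force. If the text is followed as written, the reported accuracy of the LVO model will tend to be too high: the same patients serve every modelling step and the scoring, and phases 3 and 5 validate only the mimic models.

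A reader might settle on one size, such as 0.05 to 0.09 in AUC. The documents do not support that: it matches about 22 LVO cases with 12 candidates, and the article gives neither number. The defensible statement is a range: roughly 0.02 to 0.14 for 22 to 45 cases and 8 to 20 candidates, and about 0.01 to 0.055 for 75 to 100 cases. These figures assume independent normal predictors and AIC elimination. A stricter AUC test would keep fewer variables and could change them.

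That LVO cases will be few is likely but inferred. Priority is low to moderate: the substudy is exploratory, and neither the main objectives nor the sample size depends on it.

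**What to change.** For sub-study objective 2, report bootstrap optimism-corrected AUC, sensitivity and specificity beside the apparent values. Repeat transformation, variable selection, fitting and threshold choice in each resample, so that the correction covers the whole procedure. Use confidence intervals that reflect those steps. Define the AUC selection rule closely enough to be programmed, which the bootstrap needs in any case. Report the number of LVO cases and the number of candidate predictors. Base any statement about the promise of LVO detection on the corrected figures.

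If the unseen analysis plan already provides this, one sentence saying so is enough. The cost is a little more analysis work and less favourable reported accuracy. No further patients or data are needed.

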### Study monitoring, quality control and quality assurance

The chief investigator will have overall responsibility for study conduct. The local principal investigators will be responsible for the day-to-day study conduct at their individual NHS sites. The study will be managed by a coordinating centre based at Newcastle University who will provide training and day-to-day support for the sites. Quality control will be maintained through adherence to the Newcastle Biomedicine Clinical Research Platform standard operating procedures, the study protocol and research governance regulations. The study may be subject to inspection and audit by the Northumbria Healthcare NHS Foundation Trust under their remit as sponsor. A Study Steering Committee will be convened to provide oversight of the trial. This will comprise of the study investigators plus an independent member. This committee will aim to meet 6 monthly.

### Dissemination of results

The study will be presented at national and international conferences and reported in peer-reviewed journals. Reports will be written for the study funder, sponsor and regulatory bodies. A lay summary of the results will be available for study participants.

## Discussion

Early diagnostic uncertainty about the cause of suspected stroke symptoms results in displacement of non-stroke mimic patients from more appropriate services, inappropriate demands on specialist resources and delayed access to specialist care and time-critical reperfusion therapies for stroke patients. Blood biomarkers have not previously been shown to be useful in emergency stroke assessment due to delayed elevation and a need for complex assays [13–15]. In addition, markers of inflammatory response or vascular risk have not improved upon clinical assessment alone [13, 28]. However, there is now evidence to suggest that blood purine concentration which rises rapidly during hypoxic tissue injury may be able to assist with urgent differentiation of stroke from mimic conditions [16–19].

This study will determine the performance of a portable point of care fingerprick measurement of blood purine concentration for the identification mimic patients within the suspected stroke population. We will also consider whether blood purine readings show greater diagnostic accuracy when combined with other information available to clinicians such as symptom severity. A substudy will explore whether serial purine readings could be an early indicator of large vessel occlusion which could be an alternative use of the test.

If test performance to identify non-stroke mimic conditions is satisfactory, future deployment in ambulances and emergency departments could assist with urgent triage of patients with suspected stroke symptoms and enable more appropriate direction of patients to stroke or non-stroke services. Improved service access could consequently result in better outcomes through faster access to appropriate treatments.

## Study status

At the time of submission of this manuscript, recruitment to the hospital cohort is in progress. Protocol version 4 dated 14 July 2020 was used to prepare this manuscript.

## Data Availability

Not applicable

## Abbreviations

AVPU: Alert, Voice, Pain, Unresponsive
CRF: Case record form
CT: Computerised tomography
CTA: CT angiogram
CTP: CT perfusion
FAST: Face Arm Speech Time
HASU: Hyperacute stroke unit
LVO: Large vessel occlusion
MRA: MR angiography
MRI: Magnetic resonance imaging
MT: Mechanical thrombectomy
NHS: National Health Service
NIHSS: National Institute of Health Stroke Scale
NNT: Number needed to treat
PI: Principal investigator
ROC: Receiving operating curve
STARD: Standards for the Reporting of Diagnostic Accuracy Studies
TIA: Transient ischemic attack
WBPC: Whole blood purine concentration
